**Sleep, health and physical activity**								
Actigraphy		✓	✓	✓		✓	✓	✓
Sleep quality		✓	✓	✓		✓	✓	✓
**Questionnaires**								
Big life sodium calculator		✓		✓		✓		✓
Epworth Sleepiness Scale		✓		✓		✓		✓
Geriatric Depression Scale		✓	✓	✓		✓	✓	✓
Global Physical Activity Questionnaire		✓						
Memory Assessment Clinic-Q		✓				✓		
Mediterranean Diet Serving Score		✓						
Pittsburgh Sleep Quality Index		✓						
Perceived Stress Scale		✓		✓		✓		✓
Short Form-36		✓		✓		✓		✓
State-Trait Anxiety Inventory		✓		✓		✓		✓
STOP-Bang		✓	✓	✓		✓	✓	✓
Beck’s Depression Inventory		✓						

Abbreviations: ECG: electrocardiogram; MRI: magnetic resonance imaging; AGE: advanced glycation end-products.

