The secondary outcomes are: Cannabidiol levels in peripheral blood sample.Safety (via blood biomarkers, #8 and tolerability (via adverse event reporting).Calories burned, total sleep time, number of awakenings—Physical activity and sleep quality (actigraphy) will be monitored via a wrist-based health and fitness tracker FitBit (Fitbit Inc., San Francisco, CA, USA) with a large organic light-emitting diode screen featuring heartrate monitoring and tracking of steps, distance, calories burned, floors climbed, active minutes, and sleep duration. These devices have been well-validated against gold-standard measures with good accuracy [11].Pulse wave velocity, augmentation index, and total peripheral resistance measured by Schiller BR-102 plus PWA (Schiller AG, Baar, Switzerland).Volume of hippocampus and internal carotid artery blood flow—Volume of hippocampus will be assessed by magnetic resonance imaging (MRI), T1-MPRAGE sequence, whereas blood flow through internal carotid artery will be measured by 1.5T MRI, 4D flow.Heart rate variability measured by Schiller medilog^®^AR Holter recorder (Schiller AG, Baar, Switzerland).Cardiovascular risk assessed by tissue levels of advanced glycation end-products (AGEs)—The AGE Reader (DiagnOptics Technologies BV, Groningen, The Netherlands) is a non-invasive monitoring device that uses ultra-violet light to excite autofluorescence in human skin tissue. The autofluorescence reflects tissue levels of AGEs [12]. The measurement of AGEs provides an immediate cardiovascular risk prediction in 12 s. The AGE Reader has been designed for patient-friendly diagnosis; the method is convenient, easy to use, and extensively validated.Circulating levels of blood biomarkers—Circulating (steady-state) plasma concentrations of CBD, inflammation (including TNF-alpha, IL-6, IL-10, whole blood count, etc.) and gold-standard biomarkers of plasma nitric oxide (plasma nitrite, s-nitrosothiols, and total nitric oxide) will be measured from peripheral blood sample. Lipids (cholesterol, high- and low-density lipoprotein, and triglycerides), glucose, insulin, HbA1C, renal (creatinine), hepatic (ALT, AST, ALP, GGT, and total bilirubin), drug toxicity (acyl glucuronide), and cardiovascular disease markers (hs-CRP) will also be measured.Outcomes assessed using questionnaires:

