Salt intake measured by Big life sodium calculator [13]Sleepiness measured by Epworth sleepiness scale [14]Geriatric depression measured by Geriatric depression scale-short form [15]Physical activity measured by Global Physical Activity Questionnaire (Total weekly Metabolic equivalent of task (MET)-min is calculated in a following manner: (Minutes engaged in moderate-intensity activity each week X 4 MET) + (Minutes engaged in vigorous-intensity activity each week X 8 MET) [16]Memory measured by Memory Complaint Questionnaire [17]Sleep quality measured by Pittsburgh sleep quality index [18]Perceived stress measured by Perceived stress scale [19]General health measured by Short form-36 (SF-36) [20]Anxiety measured by State-Trait Anxiety Inventory [21]Obstructive sleep apnea risk measured by STOP-BANG [22]Depression measured by Beck’s Depression Inventory [23]Mediterranean diet serving score [24]

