### 2.5. Laboratory Visits

The initial screening visit was comprised of initial assessment of anthropometrics (height, weight, waist and neck circumference), blood pressure and relevant vital signs, assessment of eligibility for study participation, and obtaining the past medical history. A total of 117 volunteers were screened, 15 patients did not meet the inclusion criteria and 30 patients met the exclusion criteria. After the completion of the screening procedures, eligible participants were randomly assigned to one of the two experimental groups. Following randomization, participants will undergo their first set of physiological, neuroimaging, sleep, and cognitive assessments. Additionally, participants will complete several lifestyle and psychological questionnaires (Table 2). This battery of assessments will be completed again following 2.5 weeks and after 5 weeks, and then repeated immediately after the washout period, 2.5 weeks after that, and 5 weeks after finishing the washout period. There will be 6 experimental visits in total to the laboratory, with additional 4 visits to the MRI suite (in selected subjects that will undergo neuroimaging). Participants will report to the laboratory after an overnight fast (>10 h) and around 07:30. Of note, subjects will be reminded to not perform exercise or to consume alcohol 24 h prior to the next visit. Water intake will be measured and allowed *ad lib*. During each experimental visit, a sample of venous blood will be taken from the forearm (cubital vein) using a sterile disposable needle and a previously cleansed skin surface. All blood samples will be procured in the early morning visit, prior to consuming the CBD or placebo capsules. This procedure will be performed by a trained laboratory technician. A maximum of 3 to 22 mL of blood will be drawn. Part of the sampled blood will be sent for immediate analysis, whereas part of the sample will be aliquoted and stored on −80 °C for subsequent analysis of biomarkers. All blood samples will be analyzed in the same certified institutional biochemical laboratory, by using the standard operating procedures. In addition, a sample of urine will be collected and stored for analysis of CBD and its metabolites with LCMS in plasma and urine.

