Following the extraction of the initial blood sample, subjects will be evaluated using bioelectrical impedance scale Tanita DC-360 S (Tanita, Tokyo, Japan) and AGE Reader and then instrumented with the 24-h ambulatory blood pressure monitor that will be used to assess continuous blood pressure measurements away from the laboratory. The device will be set to take measurements every 30 min through the day (08:30–23:00) and every hour through the night (23:00–8:00). Subjects will be also instrumented with 24-h ECG monitor. Subjects will also be asked to wear a Fitbit activity and sleep monitor. Finally, prior to discharge, subjects will be given an appropriate set of questionnaires. Apart from the bioelectrical impedance analysis which will be performed only during experimental visit 1 and 4, and AGE Reader measurement, which will be performed during visits 1, 3, 4, and 6, the protocol will be the same for all experimental visits. The whole procedure will take about 40 min per visit.

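### Section 2.5 and Table 2 give different schedules for declared secondary outcomes; if Table 2 is followed, six of them have no on-treatment value

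*Protocol article*

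**What the plan says.** Section 2.4 lists these among the secondary outcomes:

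- "Cardiovascular risk assessed by tissue levels of advanced glycation end-products (AGEs"), read by the AGE Reader
- "Sleep quality measured by Pittsburgh sleep quality index"
- "Depression measured by Beck’s Depression Inventory"
- "Memory measured by Memory Complaint Questionnaire"
- "Physical activity measured by Global Physical Activity Questionnaire"
- the Mediterranean diet serving score

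Section 2.5 introduces the physiological, imaging, sleep and cognitive assessments and the lifestyle and psychological questionnaires. It then states: "This battery of assessments will be completed again following 2.5 weeks and after 5 weeks", with the same pattern after the washout. Later it names two exceptions to an otherwise identical protocol at all six visits. One is bioimpedance, at visits 1 and 4. The other is the "AGE Reader measurement, which will be performed during visits 1, 3, 4, and 6".

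Table 2 ticks AGE Reader, "Pittsburgh Sleep Quality Index", Beck's Depression Inventory, the Global Physical Activity Questionnaire and the Mediterranean diet score at week 0 of the first set of visits and nowhere else. The memory questionnaire is ticked at week 0 of each set and nowhere else.

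**The concern.** Comparing CBD with placebo requires a value taken while participants are on each treatment. An outcome measured only before treatment starts cannot show a treatment effect, whatever the sample size or model. Section 2.9 leaves the secondary analyses and the handling of missing data to a later plan, but no analysis plan can recover a measurement that was never scheduled. The article therefore carries two schedules with very different consequences: one supports a comparison on these six outcomes and the other rules it out. A reader cannot tell which one applies.

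**Working it through.** No power or sample-size figure bears on this point. The check is a count of scheduled measurements.

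**Column mapping.** Table 2 has weeks 0, 2.5 and 5 in each of two sets of visits, which are visits 1 to 3 and 4 to 6. The bioimpedance row confirms this: section 2.5 says visits 1 and 4, and Table 2 ticks week 0 of both sets. Week 0 of the second set comes straight after the two-week washout and before second-period treatment, so it is off treatment. The on-treatment columns are therefore weeks 2.5 and 5 of each set: 2 × 2 = 4.

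**Count for the six outcomes.**

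| Secondary outcome (section 2.4) | Ticks in Table 2 | On-treatment values, Table 2 | On-treatment values, section 2.5 |
|---|---|---|---|
| AGE Reader | week 0, first set | 0 | 2 (visits 3 and 6) |
| Pittsburgh Sleep Quality Index | week 0, first set | 0 | up to 4 |
| Beck's Depression Inventory | week 0, first set | 0 | up to 4 |
| Global Physical Activity Questionnaire | week 0, first set | 0 | up to 4 |
| Mediterranean diet score | week 0, first set | 0 | up to 4 |
| Memory questionnaire | week 0, both sets | 0 | up to 4 |

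The table's row is called Memory Assessment Clinic-Q. Matching it to the memory questionnaire of section 2.4 is an inference, but each is the only memory instrument in its list.

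**Count for the rest.** Of the twelve questionnaires, two have four on-treatment ticks (Geriatric Depression Scale, STOP-Bang). Five have two (sodium calculator, Epworth, Perceived Stress Scale, SF-36, State-Trait Anxiety Inventory) and five have none: 2 + 5 + 5 = 12. The other cardiovascular, laboratory and sleep rows have two or four. Bioimpedance also has none, but it is not a declared outcome and the text agrees with the table. All the cardiovascular, laboratory, sleep and questionnaire rows checked carry the same number of columns, so lost ticks are an unlikely explanation.

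**Consequence if Table 2 is followed.** The number of participants with a value under both CBD and placebo is 0 for each of the six. This holds whether the trial has 70 participants (section 2.1) or 72 (section 2.6). If section 2.5 is followed, it is up to that full number. A first-period comparison between groups does not help, because the only value precedes treatment. The second memory score, taken after washout, could show at most a residual difference between the two sequences.

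**What is not lost under Table 2.** 24-h ambulatory blood pressure is ticked at all six visits. Among the psychological scales, the Geriatric Depression Scale has four on-treatment values, and the Perceived Stress Scale, SF-36 and State-Trait Anxiety Inventory have two each.

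**The case against.** The strongest reply is that Table 2 governs the questionnaires and its single ticks are deliberate. Section 2.5 refers to Table 2 where it introduces them, and later speaks only of giving participants a suitable set, which may vary by visit. The statement that the battery is repeated cannot be a literal item-by-item schedule, because five other questionnaires, MRI and the blood biomarkers also lack a 2.5-week tick. This stands in part: the text does not contradict the table as firmly for the five questionnaires as for AGE Reader. Some tension remains, because section 2.5 names only two exceptions to an identical protocol. If the table does govern, declared secondary outcomes have no on-treatment value.

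The physical activity and diet scores may well be baseline descriptors, since section 2.3 asks participants to keep activity and food intake at visits 2 to 6 as at visit 1. That is plausible. The fault would then be their place in the outcome list.

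A Sleep quality row in Table 2 is ticked at all six visits. Section 2.4 uses that term both for actigraphy and for the Pittsburgh index. Because the Pittsburgh index has its own single-tick row, the other row does not clearly rescue it, but the overlap is a real ambiguity.

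A reader might infer that no CBD effect on these six outcomes can be estimated, or that the psychological well-being aim fails. The documents support neither. The first holds only if Table 2 is the schedule in use, since section 2.5 provides on-treatment values. The second is wrong even under Table 2, because four psychological scales are measured on treatment. Memory and tissue AGEs are not named in the aims set out in the introduction, though Table 2 offers no other on-treatment measure of either.

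**Conclusion.** The text and the table are inconsistent and need to be reconciled. For AGE Reader the contradiction is explicit: four visits in section 2.5, one in Table 2. For the Pittsburgh, Beck and memory instruments the schedule is unclear, and Table 2 as printed does not match their status as secondary outcomes. For the physical activity and diet scores, misclassification is the likelier explanation.

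The size is six declared secondary outcomes with 0 on-treatment values under the table, against 2 (AGE Reader) or up to 4 (questionnaires) under the text. The loss is conditional on Table 2 being followed. The full protocol is not shown and may already settle the matter. The primary outcome is untouched and the well-being aim is still served, so this is a should-fix.

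**What to change.** 1. **AGE Reader:** tick weeks 0 and 5 of both periods in Table 2, as section 2.5 already states.
2. **Pittsburgh, Beck and memory questionnaires:** schedule them at week 5 of both periods, on the weeks 0 and 5 pattern that Table 2 uses for the Perceived Stress Scale, SF-36 and State-Trait Anxiety Inventory. Reword the repeated-battery sentence in section 2.5 so that it no longer implies every item at 2.5 weeks. Otherwise, remove these instruments from the secondary outcomes.
3. **Physical activity and diet scores:** if one measurement is intended, list them as baseline descriptors.
4. **Sleep quality row:** state whether it means actigraphy or the Pittsburgh index.

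The cost is small. On the full weeks 0 and 5 pattern, the added ticks per participant are 3 (AGE Reader) + 3 (Pittsburgh) + 3 (Beck) + 2 (memory) = 11, all at visits already planned. Section 2.4 puts an AGE reading at 12 seconds. Section 2.5 reports screening and randomisation in the past tense, so this is time-sensitive: missed week-5 values cannot be recovered. For visits already completed, record which schedule was used and report those outcomes accordingly.

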## Data Availability

The data presented in this study are available on request from the corresponding author. The data are not publicly available because some of the dataset will be used for further research.
